### Other outcomes

Adherence will be monitored through the records computed by the app and confirmed during the weekly calls to the TG. Participants who perform all the proposed exercises at least three times a week will be considered fully adherent.

Adverse events will be monitored weekly during phone calls and will be reported in the study results. Adverse events are those harmful or unfavorable results that occur during or after exercise [64], such as nausea, headache, falling, and incapacitating pain. Events not related to the intervention will also be monitored. Participants who report a serious adverse event will be instructed to seek emergency medical services. The intervention will be interrupted if the adverse event makes it impossible for the participant to perform physical exercises.

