Telerehabilitation may be a viable alternative to reduce the waiting time for physical therapy [16], minimizing the negative impacts of inactivity, such as falls [17], sedentary pattern [18], and loss of strength, mobility, and resistance [19]. Telerehabilitation provides rehabilitation through information and communication technologies such as videoconferencing, telephoning, and smartphone app [20–22]. This rehabilitation modality offers early access to treatment, reduces costs (mostly with transportation), induces the patient to play a more active role in the treatment, and allows the treatment to be adapted to their routine [16, 23–26]. Evidence shows that telerehabilitation is safe [27, 28], effective, and less costly when compared to face-to-face rehabilitation [23, 25, 26]. In patients who underwent orthopedic surgery, telerehabilitation had positive effects on physical function [28, 29], range of motion [30], function, and pain [31]. In addition, the face-to-face and telerehabilitation modalities demonstrated equivalent results for hospital discharged patients [32–37]. More recently, the social isolation resulting from the COVID-19 pandemic has shown that distance healthcare is essential to ensure treatment continuity, especially for older adults [38]. Therefore, investing in programs that reduce costs without compromising the population’s access is essential.

This paper presents the protocol for a pragmatic superiority clinical trial that aims to determine the effectiveness and cost-effectiveness of a personalized exercise program offered by telerehabilitation to minimize the deconditioning of older adults who are, for non-specific conditions, awaiting outpatient physical therapy.

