### Control group

CG participants will follow the usual flow of the waiting list of patients awaiting outpatient physical therapy in the public healthcare system and will not receive any guidance or exercise, as recommended in pragmatic studies. They will be monitored weekly by telephone call to check the onset of outpatient physical therapy and adverse events. Like the TG, the period each CG participant will spend in the trial will depend on the time awaiting outpatient physical therapy. Participants in both the TG and CG will not be prohibited from receiving others interventions such as exercises on their own, physical activity (e.g., walking), medications, or physical therapy elsewhere while on the waiting list, but this information will be recorded.

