### Economic evaluation

The economic evaluation will be carried out from the perspective of society and the Brazilian public healthcare system during the study period. The costs will be reported based on values updated to the year of data collection. In this phase, all information will follow the recommendations of the Brazilian Ministry of Health’s Methodological Guidelines for Economic Evaluation [63]. Cost measures will be obtained by estimates of health service utilization (public and private) due to the health condition that caused the referral to outpatient physical therapy and/or generated adverse events. The app development costs will be excluded.

The costs to the public healthcare system will be measured based on the use of health services and procedures reported by participants by the weekly Google form platform, and these data will only be assessed by researchers blinded to group allocation. The costs for hospital care, elective consultations, outpatient or home physical therapy, and medication will be included. These costs will be valued using standardized cost tables of the Brazilian public healthcare system.

Costs to society will include direct costs to participants and caregivers and loss of productivity. The calculation of direct expenses, such as medication, purchase of equipment, transportation, hiring caregivers, and health services will be based on surveys answered by participants. The cost of transportation will be evaluated by the distance between the participant’s home and the physical therapy site, adjusted by the type of transportation used and the price of gasoline. Information on the loss of productivity will be obtained for participants and non-contracted caregivers (e.g., family members) through surveys administered to participants who will indicate whether they have paid work, income from this work, and lost workdays due to the health condition.

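### The adverse event definition is tied to exercise, which only one arm is assigned, and the plan does not say whether other monitored events are reported or costed

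*Protocol article*

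**What the plan says.** Other outcomes defines the term: "Adverse events are those harmful or unfavorable results that occur during or after exercise". Nausea, headache, falling and incapacitating pain are its examples. The same paragraph promises that "Adverse events will be monitored weekly during phone calls and will be reported in the study results", and adds that "Events not related to the intervention will also be monitored".

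Under Control group, controls "will not receive any guidance or exercise, as recommended in pragmatic studies". The section also says of them: "They will be monitored weekly by telephone call to check the onset of outpatient physical therapy and adverse events". Participants in both groups "will not be prohibited from receiving others interventions such as exercises on their own, physical activity (e.g., walking), medications, or physical therapy elsewhere", and such activity is recorded.

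Under Economic evaluation, the health service use that is counted is use "due to the health condition that caused the referral to outpatient physical therapy and/or generated adverse events". Other outcomes contains the article's only definition of an adverse event.

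**The concern.** Whether an event counts as adverse depends on whether the person had exercised, and exercise is what allocation changes. One arm is assigned sessions three to five times a week and the other none. A definition that depends on the assigned exposure can produce different counts in two arms with the same underlying risk, even if every participant is asked the same questions on the weekly call.

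Two results could be affected. The first is the adverse event report. The Background describes telerehabilitation as "minimizing the negative impacts of inactivity, such as falls", so a fall during an inactive wait is an event that a reader would expect to see in the control column. The second is the economic evaluation, whose inclusion rule uses the same term. The Discussion hypothesises lower costs and suggests fewer readmissions. If event-related care in inactive controls is left out, part of the hoped-for saving is not counted.

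**Working it through.** The article gives no event rates and no event costs. The sample size of 115 per group has no bearing on this point. The check is therefore a reading of the sections together.

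**Step 1: apply the wording to the same event in different circumstances.** Take a fall that leads to an emergency visit and is unrelated to the referral condition.

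| Case | Inside the definition? | Reporting stated? | Cost counted, if the clause takes this definition? |
|---|---|---|---|
| Telerehabilitation, after a programme session | Yes | Yes | Yes |
| Control, no exercise beforehand | No | Monitoring only | No |
| Control, after exercise on their own | Yes | Yes | Yes |
| Telerehabilitation, no exercise beforehand | No | Monitoring only | No |

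The wording does not classify by arm directly. It classifies by exercise, and allocation shifts how often each row occurs. The last row may also be rare in practice. The article sets no time limit on what counts as after exercise, so in someone training three to five times a week many events could be placed in the first row.

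**Step 2: compare with the control monitoring.** Controls are called weekly to check for adverse events. For a control who does not exercise, that check has almost nothing to find under the definition. The two sections fit together only if a wider meaning is intended in one of them.

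**Step 3: see whether the sentence on unrelated events closes the gap.** It establishes that these events are monitored. It does not say that they are adverse events, that they are reported, or that they are costed.

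**Step 4: trace the cost rule.** Care due to the referral condition is counted in both arms whatever the definition. Only care for other events depends on the adverse-event clause. That clause does not refer to Other outcomes, so the cost asymmetry is possible but not fixed by the text.

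**Step 5: express the size.** Let r_T and r_C be the true event risks in the two arms, and q_T and q_C the shares of those events that meet the definition. If only events meeting the definition are reported:

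- counted risk = q_T × r_T in telerehabilitation and q_C × r_C in control;
- counted risk ratio = (r_T / r_C) × (q_T / q_C).

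The distortion is the factor q_T / q_C. It equals 1 if the shares are equal, or if all monitored events are reported (both shares then equal 1). It exceeds 1 when events in the exercising arm more often follow exercise, and has no upper limit as q_C approaches 0. The article gives none of the four quantities, so no value can be put on it.

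**The case against.** The case against is substantial, and most of it limits the point.

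- **Controls can have adverse events.** A reader might infer that they cannot, so that their count must be zero. The article does not support this: controls may exercise, walk or have physical therapy elsewhere, and the definition does not confine exercise to the trial programme.
- **Other events are captured.** Both arms are called weekly and unrelated events are monitored. This stands for capture. It does not settle what is reported or costed.
- **No safety comparison is promised.** A reader might infer that a formal between-arm comparison would be reversed. The article states no such comparison or test, and falls are neither a primary nor a secondary outcome. A reversal would need assumed fall risks and a control count at or near zero.
- **The cost rule is not expressly linked to the definition.** Referral-condition care is counted in both arms, and researchers blinded to allocation assess the service-use data. A cost asymmetry needs an event unrelated to the referral condition, no prior exercise, and the strict definition carried over. Blinding would not remove it, because it would arise from what the rule includes.
- **A journal article condenses.** Event forms and by-arm tables may stand in the full protocol or analysis plan, so their absence is no finding. The definition, however, is stated here, and it does not fit the control monitoring described in the same article.

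**Conclusion.** The point holds as a defect in a stated definition. The meaning of an adverse event depends on exercise, only one arm is assigned exercise, and the other arm is nonetheless monitored for the same term. The article leaves open whether the separately monitored events are reported as adverse events or enter the adverse-event cost clause. Ascertainment of reported events may therefore differ by arm, and so may event-related costs outside the referral condition.

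If the wording is applied literally and events more often follow exercise in the telerehabilitation group, the tilt is against telerehabilitation. Its size cannot be calculated from the article. If the investigators already intend to report and cost all monitored events alike in both arms, only the wording needs repair. The text does not show a demonstrated bias or a certain reversal. The correction is still worth making, because it is cheap and removes the dependence on exposure.

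**What to change.** In Other outcomes, define an adverse event as any untoward medical event from randomisation onward, whether or not the participant exercised, with the same event list and the same period in both arms. Record relation to exercise or to the intervention as a separate field. State that all events will be reported by arm. In Economic evaluation, state that the adverse-event clause uses this definition.

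This takes one revised definition, one extra field on the weekly call form and one cross-reference. Both arms already receive the calls, so no contact is added. The downside is that more events will be recorded in both arms, including unrelated ones. The change concerns recording, reporting and costing only, and leaves clinical management rules as they are.

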### Sample size

The sample size was based on the TUG primary outcome. An effect size of d=0.4, previously obtained by Brovold et al. (2012) [65], power of 80%, alpha of 0.05, and abandonment rate of 15% were considered to estimate sample size using the G*Power 3.1 software. This resulted in a minimum sample size of 230 participants, 115 per group.

### Data analysis plan

The outcome variables and the participants’ characteristics will be analyzed with descriptive statistics. The Kolmogorov-Smirnov test will be used to test the normality of the data. Comparison of TG and CG baselines will be conducted with parametric or non-parametric test.

Outcome group comparisons will be analyzed with the nonlinear mixed effect model [66], given that deconditioning follows a nonlinear path over time and the period individuals remain in the study is not homogeneous. Since the intervention time will be different among the participants, time will be treated as a random factor.

All data will be analyzed for intention-to-treat; that is, all random participants will be included in the analysis regardless of adherence to the protocol. The data will be analyzed by the R software (R Foundation for Statistical Computing, Vienna, Austria) with a significance level of 5%.

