### Randomization and allocation

After the initial evaluation, participants will be randomly allocated to the following groups: telerehabilitation (TG) and control (CG). The allocation will be in random blocks sizing four and six, with an allocation rate of 1:1. The randomized sequence will be computer-generated before the start of the study by a researcher not involved in the study and placed in opaque, sealed, sequentially numbered envelopes. This sequence will remain concealed until the participant is allocated to the groups.

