### Data collection

Figure 2 shows the schedule of enrollment, interventions, and assessments (according to the SPIRIT). Outcomes will be assessed by in-person meetings at baseline (t0), at the end of the telerehabillitation protocol (t1), and after discharge from outpatient physical therapy or within 6 months of outpatient treatment (t2). All evaluations will be performed by a trained evaluator blinded to group allocation. All instruments show adequate validity and reliability for older adults [48–52].

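### Unequal waiting times do not justify treating time as a random factor, and the stated nonlinear model leaves the group difference at the end of the wait (t1) unspecified

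*Protocol article*

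**What the plan says.** The Data analysis plan names the model and gives its reason: "Outcome group comparisons will be analyzed with the nonlinear mixed effect model [66], given that deconditioning follows a nonlinear path over time", adding that time in the study is not the same for everyone. It then assigns time its role: "Since the intervention time will be different among the participants, time will be treated as a random factor". It names no fixed time term, group-by-time term or primary time point. It also says of baseline: "Comparison of TG and CG baselines will be conducted with parametric or non-parametric test".

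The Data collection section sets three visits. "Outcomes will be assessed by in-person meetings at baseline (t0), at the end of the telerehabillitation protocol (t1"), and the third (t2) comes at discharge from outpatient physical therapy or within 6 months of that treatment. Visit t1 may fall up to one week into outpatient therapy. Randomization follows the baseline evaluation, and the intervention ends when the participant is called to outpatient therapy (Randomization and allocation; Telerehabilitation intervention). The hypothesis in the Discussion is that the programme limits deconditioning in patients who are waiting.

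**The concern.** The article makes an explicit choice about time and gives a reason that does not lead to it.

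- **Role of time.** A random effect for time says how much people or occasions vary. The treatment effect is a fixed quantity: the difference between groups at a given time. If waits differ, elapsed or waited time belongs in the fixed part of the model; a random slope may be added to it but cannot replace it.
- **Target.** The hypothesis concerns the wait, so t1 is the visit that answers it. At t0 the expected group difference is zero by randomization. At t2 both arms have had outpatient therapy.
- **Shape.** Two visits bound the wait. Two points per person cannot show a person's nonlinear path, and one smooth curve through t2 runs across a change of treatment at t1.

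At stake is whether the primary result answers the trial's question. The text as it stands is compatible with analyses of very different power, and its one explicit statement about time points away from the t1 contrast.

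**Working it through.** **1. Reproduce the planned sample size.** Inputs from the Sample size section: "An effect size of d=0.4"; "power of 80%, alpha of 0.05, and abandonment rate of 15% were considered". Allocation is equal ("with an allocation rate of 1:1"). Sidedness is not stated; two-sided is assumed.

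- A two-sample t-test needs 100 per arm (power 80.4%), 200 in total.
- 200 × 1.15 = 230, which matches: "This resulted in a minimum sample size of 230 participants, 115 per group". (Dividing instead, 200/0.85, gives 236.)
- Completers per arm: 115 × 0.85 = 97.75, taken as 97. Power for d = 0.4 is then 79.2%.

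The sample size therefore corresponds to a simple two-group comparison at one time point, not to a nonlinear mixed model over three visits.

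**2. Illustration: no group-by-time term.** Suppose the only treatment term is one group coefficient averaged equally over the visits. Let the effect be 0 at t0, 0.4 SD at t1 and e2 at t2, with e2 assumed between 0 and 0.4. The expected estimate is (0 + 0.4 + e2)/3. The SD of a three-visit mean is √((1 + 2ρ)/3), where ρ is the between-visit correlation: 0.816 at ρ = 0.5 and 0.931 at ρ = 0.8. Power ≈ Φ(d·√(97/2) − 1.96), with d = estimate/SD and √(97/2) = 6.964.

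| e2 (assumed) | Expected estimate | Dilution | Power, ρ = 0.5 | Power, ρ = 0.7 | Power, ρ = 0.8 |
|---|---|---|---|---|---|
| 0 | 0.133 | 67% | 20.5% | 17.8% | 16.8% |
| 0.2 | 0.200 | 50% | 40.0% | 34.4% | 32.1% |
| 0.4 | 0.267 | 33% | 62.3% | 54.6% | 51.4% |

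Example: 0.133/0.816 = 0.163; 0.163 × 6.964 − 1.96 = −0.82; power 20.5%.

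**3. Other readings of the model.**

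- Random slope in time, still without group-by-time (intercept variance 0.6, residual 0.4, slope adding 0.2 or 0.8 at the last visit; visits at 0-1-2, 0-2-5 or 0-3-9): baseline takes 41% to 58% of the weight, and dilution is 41% to 67%.
- Baseline as covariate, one group effect over t1 and t2: (0.4 + e2)/2 = 0.2 to 0.4, so dilution is 0% to 50%.
- Fixed group-by-visit term, read at t1: dilution 0%.

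A mixed-model simulation (98 per arm, ρ = 0.7, visit fixed, 150 replicates) agrees. The single group coefficient averaged 0.15, 0.21 and 0.26 for e2 = 0, 0.2 and 0.4. The group-by-t1 term averaged 0.40 to 0.41.

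**4. Power of the t1 contrast at 97 per arm.** Unadjusted: 79.2%. Adjusted for baseline, d = 0.4/√(1 − ρ²):

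- ρ = 0.5: 0.4/0.866 = 0.462, power 89.6%
- ρ = 0.7: 0.4/0.714 = 0.560, power 97.4%
- ρ = 0.8: 0.4/0.600 = 0.667, power 99.6%

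**The case against.** The strongest reply is that the article does not say time is only random. In a nonlinear mixed model the mean is a function of time, groups can be compared through the parameters of that curve, and the sentence may mean participant-specific time effects added to it. Fixed terms, contrast and covariates may stand in a fuller plan that is not shown. This stands, and it rules out a stronger reading. A reader might infer that the planned analysis dilutes the effect by a third to two thirds, or has 17% to 62% power. Those figures describe a model without group-by-time and with equally weighted visits, which the article does not state.

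Three further inferences also go too far:

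- **The model will fail to converge.** No nonlinear model was fitted to test this. Because waits differ, t1 falls at different elapsed times and gives some information on a population curve. That support is weak, but estimation is not impossible.
- **Correcting the role of time raises power from about 79% to 90% or more.** That gain comes from baseline adjustment at an assumed correlation. A longitudinal model that includes t0 as an outcome may already use part of it.
- **Baseline tests replace adjustment.** The article does not say so. Such tests only check chance imbalance in a randomized trial; they are a minor, separate matter.

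The reply does not rescue the stated reasoning. Further detail could add a fixed part, but unequal waits would still be no reason to make time random, and the treatment change at t1 would still lie inside a curve fitted through t2.

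**Conclusion.** The point holds as a flaw in a stated choice. The Data analysis plan gives time a random role for a reason that does not support it, and as written it does not specify the t1 group difference that the hypothesis calls for. A nonlinear path within the wait cannot be estimated for individuals and is only weakly supported for the population.

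The size is conditional. The loss ranges from nothing, if a fixed group-by-visit term is fitted and read at t1, to an estimate of 0.13 to 0.27 SD in place of 0.4 under the equal-weight average. The correlations and the share of the effect persisting at t2 are assumptions; the documents give neither. The text should be changed before the data are analysed by group.

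**What to change.** Replace the model sentences with the following, for each primary outcome measure:

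- **Model.** A linear mixed model with fixed visit and fixed group-by-visit, the baseline value as covariate or constrained equal between groups, and a random participant effect or unstructured covariance. ANCOVA at t1 is the simpler alternative. The constrained form keeps every randomized participant with a baseline value in the model, which suits the intention-to-treat statement.
- **Primary contrast.** The baseline-adjusted difference, telerehabilitation minus control, at t1. The t2 difference is secondary.
- **Waiting time.** Days waited as a fixed continuous term, with group-by-days, in a secondary analysis, since the length of the wait is known only after randomization.
- **Nonlinear model.** Exploratory only.
- **Baseline (minor).** Describe the groups and drop the significance tests.

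The cost is a dated rewording of one section. No further data are needed, and N stays at 230.
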